## APPENDIX B Respiratory Distress Severity Grading Table

| Respiratory Component   | Grade 1 (Mild)                                                                                                | Grade 2 (Moderate)                                                                      | Grade 3 (Severe)                                                                                                          | Grade 4 (Potentially Life threatening)                                                                                                            |
|-------------------------|---------------------------------------------------------------------------------------------------------------|-----------------------------------------------------------------------------------------|---------------------------------------------------------------------------------------------------------------------------|---------------------------------------------------------------------------------------------------------------------------------------------------|
| Upper respiratory tract | Barky/croupy cough but able to sleep, take fluids, and play                                                   | Inspiratory upper airway sounds
OR barky cough that interferes with sleep            | Requires systemic steroids                                                                                                | Requires more than 1 racemic epinephrine
OR hospitalization OR requires medical observation for >6 hours                                       |
| Lower respiratory tract | End-expiratory wheezing                                                                                       | Wheezing through expiratory phase or requiring prn administration of $\beta_2$ agonists | Wheezing requiring systemic or nebulized steroids or nebulized $\beta_2$ agonists with a frequency of up to every 4 hours | Requires nebulized $B_2$ agonist more frequently than every 4 hours                                                                               |
| Work of breathing       | Cough lasting for more than 4 hours in any 24 hour period not associated with feed/emesis, can smile and play | Cough that prevents normal feeding or prevents sleep for more than 4 hours              | Grunting,
OR nasal flaring,
OR retractions                                                                          | Respiratory fatigue
OR respiratory rate >55 despite treatment OR tachypnea despite treatment (>60 for 1-12 month old, >55 for 12-24 month old) |
| Oxygen saturation       | Normal room air oxygen saturation 98-100%                                                                     | Abnormal room-air oxygen not requiring supplemental oxygen                              | Room air saturation <95%                                                                                                  | Requires supplemental oxygen to maintain oxygen saturation >93%                                                                                   |

prn = as the circumstances require

To be implemented for scoring the severity of MA-LRIs. The overall grading of the Upper or Lower Respiratory Tract Illness should be the highest degree of severity assigned among all the components of the respiratory event.

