#### **4.1.6 Study Reporting Period for Enhanced Disease Surveillance**

Although there is no evidence that vaccination with any live attenuated RSV candidates predisposes subjects to increased severity of disease with subsequent RSV infections, the goal of this surveillance is to evaluate the link between any severe morbidity/hospitalization and RSV infections. To monitor for possible enhanced RSV disease, laboratory confirmation of the presence or absence of RSV in respiratory secretions will be collected for all MA-LRIs. All MA-LRIs will be assessed for severity according to [APPENDIX B](#). The overall grading of a MA-LRI should be the highest degree of severity assigned among all of the components of the respiratory event detailed in APPENDIX B. Nasal samples will be collected by the investigator within 24 hours (or as soon as possible) after onset of the event and will be analyzed at a central laboratory for respiratory virus identification. The reporting period for enhanced disease surveillance is the period immediately following study vaccine administration through 365 days post randomization. In addition, information regarding oxygenation status, supplemental oxygen requirements and specific drug treatment will be collected, as well as any other concurrent respiratory illness present at the time of the diagnosis of the event.

In the unlikely event that a statistically significant difference between vaccine group and placebo group in the rate of RSV-related hospitalization or death at the end of the study follow-up period (365 days after randomization in a cohort) is observed, then the protocol and informed consent form will be amended to continue to follow enrolled subjects through an additional RSV season. For the purpose of surveillance, the following definition for RSV enhanced disease will be used: a clinically significant increase in rates of RSV-related hospitalization or death in vaccinees

compared with placebo subjects. To qualify as an RSV-related hospitalization or death, either wild-type RSV must have been identified in a clinical specimen OR a valid negative result for RSV testing was not available from a clinical specimen obtained during the window from 2 days prior to onset of symptoms to 5 days after onset of symptoms (ie, in the absence of a confirmed negative culture, events are analyzed as if associated with shedding of wild-type RSV).

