##### **Interruption or Discontinuation of Study Randomization**

If any of the following occur, the IVRS system will be locked and no additional subjects will be randomized into the study until a review of the event in question is performed by the Medical Monitor and the SMC:

1. Any MA-LRI associated with shedding of vaccine virus whether or not another respiratory pathogen has been detected

Note: If viral culture results (or, in the event that culture results are not available for technical reasons, PCR results) are not available for a nasal wash specimen collected between 2 days prior to onset through 5 days after onset, an MA-LRI event will be assessed as if associated with shedding of vaccine virus, if the MA-LRI occurs within 28 days post dose

2. The occurrence of a statistically significant imbalance (analyzed by subject) either cumulatively (ie, among all cohorts) or by cohort in Grade 3 and 4 adverse events (includes MA-LRI events) occurring within 28 days after dosing with more events in vaccine arm compared to placebo arm
3. Any event, which in the opinion of the investigator, Medical Monitor, or Unblinded Safety Physician contraindicates enrollment of additional subjects

If study randomization has been interrupted pending SMC review of event(s) while other study dosing continues, and if the SMC has found that randomization should not be re-instituted, all

study dosing also must be discontinued, unless the SMC has specifically determined that dosing may continue.

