| Event                                              | Grade 1
(Mild)                                                                                                               | Grade 2
(Moderate)                                                                                            | Grade 3
(Severe)                               | Grade 4
(Potentially Life
Threatening)                                                             |
|-----------------------------------------------------------|-----------------------------------------------------------------------------------------------------------------------------------------|--------------------------------------------------------------------------------------------------------------------------|-----------------------------------------------------------|-------------------------------------------------------------------------------------------------------------------|
| Epistaxis                                                 | Spontaneously resolves or requires <10 minutes of direct pressure                                                                       | Stops after >15 minutes of direct pressure or recurs within 24 hours                                                     | Requires nasal packing or cautery to achieve hemostasis   | Requires immediate active medical intervention to support vital functions                                         |
| Grading Adverse Event other than MA-LRI            |                                                                                                                                         |                                                                                                                          |                                                           |                                                                                                                   |
|                                                           | Transient or mild discomfort (<24 hours); no medical intervention required; symptoms cause no/minimal interference with feeding/playing | Some interference with normal activity, moderate interference with sleeping/drinking, not requiring medical intervention | Prevents daily activity and requires medical intervention | Requires significant medical attention; requires hospitalization extreme limiting of activity, medically unstable |

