| Rhonchi*                                                                         | Persistent coarse breath sounds from the lung or large airways that are not transmitted noises from the upper airway and do not clear with cough or suctioning                                                                                                                         |
| Rales*                                                                           | Persistent abnormal lower respiratory tract (eg, lung) sound heard through a stethoscope that does not clear with cough or suctioning; may be sibilant (whistling), dry (crackling), or wet, depending on the amount and density of fluid refluxing back and forth in the air passages |
| Bronchitis*                                                                      | Coarse large airway rhonchi associated with productive cough; may be accompanied by other signs of respiratory infection or may be allergic                                                                                                                                            |
| Bronchiolitis*+                                                                  | Expiratory wheezing usually associated with signs and symptoms of upper respiratory tract infection, may be confirmed by x-ray showing interstitial infiltrates and hyperinflation                                                                                                     |
| Apnea*                                                                           | Defined by history (observed by lay person) as reported cessation of breathing for 20 seconds or greater with accompanying cyanosis pallor or collapse; breath-holding spells are excluded                                                                                             |

All events require that a nasal specimen be collected within 24 hr or as soon as possible after the onset of illness or visit for medically attended respiratory illness.

\***Event/diagnosis is deemed an immediately reportable event.** In addition, all Grade 3/Grade 4 AEs are immediately reportable events, but a nasal wash specimen is required only if the Grade 3/4 event is one of the events listed in this table.

+Final diagnosis must be confirmed by the principal investigator or through confirmatory radiograph if the initial diagnosis was made by a health care provider outside the study site.

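### Appendix B, the only severity scale for MA-LRIs, grades admission only in its upper-tract row and has no cell for apnea, so an admitted lower respiratory illness can score Grade 1 or 2 and not count in the Grade 3/4 halting rule

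*Protocol*

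**What the plan says.** Section 4.1.3 lists eight diagnoses that make an MA-LRI: wheezing, pneumonia, croup, rhonchi, rales, bronchitis, bronchiolitis and apnea. Section 4.1.6 names one scale for all of them: "All MA-LRIs will be assessed for severity according to" Appendix B. The footnote to Appendix B says the same ("To be implemented for scoring the severity of MA-LRIs") and adds that the overall grade "should be the highest degree of severity assigned among all the components of the respiratory event".

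Appendix B has four rows: upper respiratory tract, lower respiratory tract, work of breathing and oxygen saturation. Admission appears once, at Grade 4 of the upper-tract row: "OR hospitalization OR requires medical observation for >6 hours". The lower-tract row runs from end-expiratory wheeze to frequent nebulized β2-agonist use and does not mention admission.

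Appendix A has a general adverse-event row whose Grade 4 reads "Requires significant medical attention; requires hospitalization extreme limiting of activity, medically unstable". Its heading limits it to events other than MA-LRIs, and the table then refers MA-LRIs to Appendix B.

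Appendix C defines apnea as "reported cessation of breathing for 20 seconds or greater with accompanying cyanosis pallor or collapse".

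Grade 4 work of breathing in Appendix B includes "respiratory rate >55 despite treatment OR tachypnea despite treatment (>60 for 1-12 month old, >55 for 12-24 month old").

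In Section 4.8, item 2 of the rules that halt randomization acts on a statistically significant excess in the vaccine arm of "Grade 3 and 4 adverse events (includes MA-LRI events) occurring within 28 days after dosing".

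**The concern.** An admission for the illness this trial watches most closely can receive a lower grade than an admission for croup or for an unrelated event. The grade then decides whether the child counts in a rule that halts randomization. That rule turns on very few subjects, so one or two grades set by a gap in the table could matter. Sites may also differ: one may apply the upper-tract hospitalization cell to any respiratory admission, while another follows the row label and does not.

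Separately, the two respiratory-rate clauses give different grades to the same treated infant.

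**Working it through.** The plan states no figure to reproduce. The check traces cases through the tables and then sizes the effect on the halting rule.

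**Step 1. Grade four cases as the tables are written.** In Appendix B the oxygen row gives Grade 1 for 98-100% and Grade 3 below 95%. Grade 2, abnormal without supplemental oxygen, is therefore in effect 95-97%.

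- *Pneumonia, admitted.* Take saturation 95-97%, no supplemental oxygen, no wheeze, grunting, flaring, retractions, fatigue or raised respiratory rate, and no steroid or nebulized β2-agonist treatment. Upper-tract row: no sign. Lower-tract row: no wheeze, so no grade. Work of breathing: Grade 1 or 2 at most, through cough. Oxygen: Grade 2. The highest is **Grade 2**.
- *Apnea, admitted,* with saturation 98-100% when measured afterwards and no other sign. No row describes apnea. The oxygen row gives Grade 1, so the highest is **Grade 1**.
- *Croup, admitted or observed for more than 6 hours.* Upper-tract row: **Grade 4**.
- *An admission that is not an MA-LRI.* Appendix A general row: **Grade 4**.

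**Step 2. Size the effect on Section 4.8 item 2.** The protocol gives no test, alpha or sidedness for this rule. Assume Fisher's exact test at 0.05, analyzed by subject, with 80 per arm (Section 5.2) and no placebo events. With k vaccine subjects against 0, the one-sided p is C(80,k)/C(160,k). With equal arms the two-sided p is twice that.

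| Vaccine v placebo | One-sided p | Two-sided p |
|---|---|---|
| 4 v 0 | 0.060 | 0.120 |
| 5 v 0 | 0.029 | 0.059 |
| 6 v 0 | 0.014 | 0.028 |

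For example, k = 5 gives (80·79·78·77·76)/(160·159·158·157·156) = 0.0293. The rule is first met at 5 v 0 one-sided or 6 v 0 two-sided. Removing one child at that point, because an admission was graded 1 or 2, gives 0.060 or 0.059, and the rule is not met.

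The threshold moves with the assumptions:

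- With one placebo event at 80 per arm it is 7 v 1 one-sided (p = 0.032) or 8 v 1 two-sided (p = 0.034).
- With both cohorts pooled at 160 per arm and no placebo events it stays at 5 (p = 0.030) or 6 (p = 0.030).
- With 20 per arm and no placebo events it is 5 v 0 on either basis (p = 0.024 one-sided, 0.047 two-sided).

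**Step 3. Compare the respiratory-rate clauses.** The first Grade 4 clause is a rate above 55 despite treatment, at any age. The second requires a rate above 60 at 1-12 months. Any rate above 60 is already above 55, so the second limit never decides a grade. A treated infant breathing at 56-60 is Grade 4 by the first clause and not by the second. Every Cohort 2 child enters below 3 months, inside that band. The bands also stop at 24 months, while a Cohort 1 child can be just under 24 + 12 = 36 months at the end of follow-up. The clause without an age limit covers such children now, so the missing band matters only if that clause is removed.

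**The case against.** The strongest reply is that Appendix B is organized by component of respiratory distress, not by diagnosis. A reader might infer that pneumonia, rales and rhonchi cannot be graded because no row names them. The table does not support that. They reach Grade 3 through grunting, flaring, retractions or saturation below 95%, and Grade 4 through fatigue, persistent fast breathing or supplemental oxygen. Appendix C notes that pneumonia usually comes with tachypnea, so the Grade 2 case above is a narrow one. This stands, and it leaves apnea and the treatment of hospitalization as the real gaps.

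Section 4.3 also asks a qualified professional to use medical judgment together with the grade categories. That may rescue some cases, but Section 4.1.6 sets the MA-LRI grade as the highest component grade, and judgment used to fill a gap can differ between sites.

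A reader might further infer that such an admission escapes safety oversight. It does not. Regardless of grade:

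- Every MA-LRI is reportable within 24 hours (4.5) and gets immediate Medical Monitor review (4.6).
- All MA-LRI hospitalizations and deaths enter the imbalance review in 4.6.
- An MA-LRI with vaccine-virus shedding halts randomization (4.8 item 1). Within 28 days of a dose, a missing virology result counts as shedding.
- An admission beyond 24 hours is a serious event (4.2.1), and a respiratory one ends that child's dosing (4.7).

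These safeguards are substantial but do not replace item 2. The shedding rule does not cover an MA-LRI with a valid negative result. A 12-hour observation for pneumonia or apnea falls short of the 24-hour hospitalization definition, yet the same observation for croup is Grade 4. The 4.6 review itself draws on severity data.

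Nor is the MA-LRI grade the criterion for enhanced disease. Section 4.1.6 defines that by rates of RSV-related hospitalization or death; severity is supporting information.

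**Conclusion.** The point holds as a defect in the grading table. Followed literally, Appendix B gives an admitted lower respiratory illness Grade 1 or 2 in the cases described, while an equal admission for croup or a non-MA-LRI event is Grade 4. Such an event would not count in Section 4.8 item 2. This takes the natural reading that the bracketed mention of MA-LRIs in that item means Grade 3 and 4 MA-LRIs; the wording could also be taken to include all of them and should be made clear.

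The effect is confined to that one rule and to severity summaries. Under the assumed Fisher test at 0.05, with 80 per arm and no placebo events, the threshold is 5 or 6 subjects. One under-graded child changes the result only when the count sits exactly at the threshold, so it would be wrong to conclude that any such child decides the rule.

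The respiratory-rate conflict is a separate inconsistency. It pushes grades up, so it does not add to the under-grading.

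**What to change.** Reconcile Sections 4.1.3 and 4.8 item 2 with Appendices A and B so that:

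- every MA-LRI diagnosis, including apnea, can be graded;
- hospitalization and prolonged observation are treated consistently across upper-tract, lower-tract and non-MA-LRI events;
- item 2 says plainly which MA-LRIs it counts.

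Reconcile the two respiratory-rate clauses and make their age bands cover the ages reached during follow-up. The sponsor's clinicians should choose the criteria and limits.

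The cost is appendix wording and site retraining. The downside is that a few more events may be reviewed as Grade 3 or 4.

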## APPENDIX C Events for Which a Nasal Wash Specimen is Required

| Event/Illness                                                                    | Definition                                                                                                                                                                                                                                                                             |
|----------------------------------------------------------------------------------|----------------------------------------------------------------------------------------------------------------------------------------------------------------------------------------------------------------------------------------------------------------------------------------|
| Within 28 days after Any Dose                                             |                                                                                                                                                                                                                                                                                        |
| Fever                                                                            | ≥100.4°F (≥38.0°C), regardless of route                                                                                                                                                                                                                                                |
| Cough                                                                            | ≥2 consecutive days of persistent cough not associated with eating or drinking                                                                                                                                                                                                         |
| Runny/stuffy nose                                                                | ≥2 consecutive days of clear or purulent discharge from the nares not associated with crying, or eating and drinking                                                                                                                                                                   |
| Breathing difficulty                                                             | Increased respiratory sounds, retractions, tachypnea, color change, grunting, nasal flaring, gasping                                                                                                                                                                                   |
| Acute otitis media (AOM)                                                         | Loss of tympanic membrane landmarks, accompanied by erythema and loss of mobility; may or may not be associated with fever or other respiratory symptoms; confirmed with tympanometry if possible                                                                                      |
| At Any Time during the Study (Day 0 through 365 days after randomization) |                                                                                                                                                                                                                                                                                        |
| Wheezing*                                                                        | Sustained high pitched, musical breath sounds, during the expiratory phase, which do not clear with cough and must be confirmed by auscultation with stethoscope; must not be transmitted upper airway sounds or inspiratory in nature                                                 |
| Pneumonia*+                                                                      | Persistent rales and crackles originating in the lower respiratory tract, usually accompanied by tachypnea, which do not clear with cough; may be confirmed by x-ray showing areas of consolidation                                                                                    |
| Croup (laryngotracheobronchitis)*+                                               | Barking cough, hoarseness, and inspiratory stridor (high-pitched whistling sound)                                                                                                                                                                                                      |
| Rhonchi*                                                                         | Persistent coarse breath sounds from the lung or large airways that are not transmitted noises from the upper airway and do not clear with cough or suctioning                                                                                                                         |
| Rales*                                                                           | Persistent abnormal lower respiratory tract (eg, lung) sound heard through a stethoscope that does not clear with cough or suctioning; may be sibilant (whistling), dry (crackling), or wet, depending on the amount and density of fluid refluxing back and forth in the air passages |
| Bronchitis*                                                                      | Coarse large airway rhonchi associated with productive cough; may be accompanied by other signs of respiratory infection or may be allergic                                                                                                                                            |
| Bronchiolitis*+                                                                  | Expiratory wheezing usually associated with signs and symptoms of upper respiratory tract infection, may be confirmed by x-ray showing interstitial infiltrates and hyperinflation                                                                                                     |
| Apnea*                                                                           | Defined by history (observed by lay person) as reported cessation of breathing for 20 seconds or greater with accompanying cyanosis pallor or collapse; breath-holding spells are excluded                                                                                             |

All events require that a nasal specimen be collected within 24 hr or as soon as possible after the onset of illness or visit for medically attended respiratory illness.

\***Event/diagnosis is deemed an immediately reportable event.** In addition, all Grade 3/Grade 4 AEs are immediately reportable events, but a nasal wash specimen is required only if the Grade 3/4 event is one of the events listed in this table.

+Final diagnosis must be confirmed by the principal investigator or through confirmatory radiograph if the initial diagnosis was made by a health care provider outside the study site.

